## Methods

### Design, setting and randomisation

The proposed study will be a single centre, early phase randomised controlled trial with observer blinding, preceded by an observational component. This design is illustrated in figure 1.

**Figure 1 F1:**
[figure not shown]
**Flowchart illustrating trial design**.

#### Study procedure

All participants will undergo baseline measurement set 1 (prognostic indicators). They will then be assessed for their ability to perform UP. Potential participants will be taken to the treatment area and shown the cycling equipment. If content to proceed, a hoist will be used to seat them on the bike safely. They will be asked to pedal slowly for one minute to familiarise themselves with the equipment. They will then be asked to pedal for one further minute and a visual observation of whether they can pedal or not will be made.

Those unable to pedal and who are 31 days or more after stroke onset will be excluded from the randomised part of this trial. Those unable to pedal and who are 30 days or less after stroke onset will be offered further pedalling assessments approximately every three days. The rationale for further pedalling assessments is that, during the first 30 days after stroke, people may experience fear of movement or emotional distress and therefore may need more than one experience of pedalling within a therapeutic environment. Without repeated opportunities for pedalling assessment some participants may be excluded unfairly from the opportunity to participate in UP.

Those participants able to pedal for one minute and who are 30 days or less after stroke onset, will then undertake baseline measures set 2 (clinical efficacy). Participants will then be allocated randomly to either routine conventional physical therapy (CPT; control group) or to CPT plus UP (experimental group). Randomisation order will be generated before the trial begins by an independent statistician, in blocks of four. Group allocation will be concealed in sequentially numbered opaque sealed envelopes held by an independent administrator, who is not involved in the study and will have no contact with study participants. The next highest number envelope will be opened by the independent administrator in response to a telephone request from the research therapist. After opening, envelopes will be stored securely with the participants' study data. Randomisation will be concealed from the independent outcome assessor and participants will be asked not to discuss group allocation with the outcome assessor.

Participants will receive their allocation intervention for up to ten minutes a day, for up to ten working days or discharge from acute stroke care, whichever occurs first. On completion of the intervention phase, participants will undertake clinical efficacy outcome measures. Every attempt will be made to undertake outcome measures even if participants withdraw or are discharged before the intervention phase is completed (intention to treat principle).

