#### Blinding

Blinding of research therapists in a therapy intervention study is not always feasible and patients are clearly aware that they are undergoing therapeutic interventions. Consequently, for this exploration of pedalling exercise, blinding of therapists and participants is not possible. However, the independent assessor of clinical outcome measures will be a trained therapist blinded to group allocation.

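### One fixed block size of four in a single-centre, open trial makes up to a third of allocations predictable to anyone who knows the block size and tracks earlier allocations

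*Protocol article*

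**What the plan says.** All references are to the protocol article.

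- **List.** Study procedure: "Randomisation order will be generated before the trial begins by an independent statistician, in blocks of four". One size is given, with no variation and no stratification. The section does not give the allocation ratio or say whether the block size is kept from the research therapist.
- **Setting.** Design, setting and randomisation: "The proposed study will be a single centre, early phase randomised controlled trial with observer blinding, preceded by an observational component". One centre and no stated strata mean one sequence.
- **Blinding.** Under Blinding, "blinding of therapists and participants is not possible"; the outcome assessor is blinded.
- **Release of allocation.** Study procedure: "The next highest number envelope will be opened by the independent administrator in response to a telephone request from the research therapist". The envelopes are opaque, sealed and sequentially numbered, and the administrator has no other part in the study.
- **Entry to the randomised part.** After a minute of familiarisation the participant is asked to pedal for one more minute, and "a visual observation of whether they can pedal or not will be made". The person who judges is not named. Those judged unable are offered another assessment about every three days while they are within 30 days of onset. Those judged able complete the set 2 baseline and are then randomised.

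**The concern.** Sealed envelopes stop anyone reading the next card. They do not stop someone working out what the card must say from the allocations already made in the same block. Here earlier allocations are visible to the treating therapists, there is only one sequence to follow, and the article itself discloses the block size.

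Predictability matters only where there is discretion over who enters and when. The pedalling judgement supplies some: a borderline participant recorded as unable is seen again about three days later, by which time someone else may have taken the predicted place.

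At stake is the balance of the arms in severity. At most 24 people are randomised, and fewer if some cannot pedal, because the Abstract counts the 24 before the pedalling attempt. The Statistical Analysis section compares follow-up scores by t-test or a non-parametric analogue, and the article states no baseline adjustment. An imbalance in starting Motricity Index could therefore carry into the primary comparison.

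**Working it through.** **Inputs from the article.** Block size 4; two arms; one centre; two recruits a month for 12 months. The article's own figure reproduces: 2 × 12 = 24. It states no figure for predictability.

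**Assumptions.** Allocation is 1:1, so each block holds two of each arm. The guesser knows the block size and every earlier allocation.

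**Share known with certainty.** An allocation is certain once one arm has used both its places. The six possible orders are equally likely.

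| Position in block | Probability that it is certain | Probability that the best guess is right |
|---|---|---|
| 1 | 0 | 1/2 |
| 2 | 0 | 2/3 |
| 3 | 1/3 | 1/3 × 1 + 2/3 × 1/2 = 2/3 |
| 4 | 1 | 1 |

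- Certain: (0 + 0 + 1/3 + 1)/4 = 1/3. Over six complete blocks that is 24/3 = 8 allocations; if only 12 people are randomised, 12/3 = 4.
- Best guess: (1/2 + 2/3 + 2/3 + 1)/4 = 17/24 = 70.8%, against 50% under simple randomisation.

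**Alternatives.** Fixed sizes were enumerated exactly. Varied sizes were simulated with lists of 24 and a guesser who knows the set of sizes and the full history but not where blocks end.

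| Scheme | Known with certainty | Best guess right |
|---|---|---|
| Fixed 4 (the plan) | 33.3% | 70.8% |
| Fixed 6 | 25.0% | 68.3% |
| Fixed 8 | 20.0% | 66.6% |
| Random 2, 4, 6 | about 4% | about 70% |
| Random 4, 6 | about 6% | about 69% |
| Random 4, 6, 8 | about 2% | about 67% |

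Varying the size removes most of the certainty but little of the advantage over a coin toss.

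**Arm sizes.** With 24 randomised, fixed blocks of four end exactly balanced. With varied sizes the last block may be cut short: the arms then differ by at most 2 (sizes 4 and 6) or 4 (sizes 4, 6 and 8), and by about 0.5 on average in both cases.

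**What steering could do.** The article gives no figure, so this is an illustration with assumed values. The leg section of the Motricity Index runs from 0 to 3 × 33 = 99. If two of 12 people in an arm scored 10 to 30 points higher than those they displaced, the arm mean would move by 2 × 10/12 = 1.7 to 2 × 30/12 = 5.0 points.

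**The case against.** The case for leaving the plan alone has substance.

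- **Safeguards are good.** There is an independent statistician, an uninvolved administrator, numbered opaque envelopes and a blinded assessor. These protect against looking ahead and against biased measurement. They do not prevent inference from past allocations, so the point survives them.
- **The pedalling verdict is not wholly unchecked.** There is a one-minute threshold. The set 2 baseline, which includes EMG during at least 30 seconds of pedalling, comes before randomisation, so a false verdict of able would meet an instrumented record. A false verdict of unable would not.
- **Holding back is not free.** Retests are only for those judged unable, so deferring someone who can pedal means recording a failure that did not happen. That would also damage the trial's second aim, predicting ability to pedal. This stands, and leaves borderline cases as the realistic route.
- **Accrual is slow.** Two recruits a month is one about every 15 days, and entry closes at day 30. Often nobody else is available for a predicted place, and deferral risks losing a participant. This restricts steering considerably.
- **The trial is early phase.** The article disclaims definitive proof of efficacy. That lowers the stakes, although the result is still meant to decide whether larger trials follow.

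A reader might infer that the research therapist will know a third of the allocations. The article does not say that this therapist is told the block size, and it does not state 1:1. A reader might also infer that the person who telephones judges the pedalling, or can move entry dates at will. The first is not stated, and the retest rule does not allow the second.

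**Conclusion.** The weakness is real but modest. Under 1:1 allocation, with complete blocks and a research therapist who knows or infers the block size and follows past allocations, one allocation in three is certain in advance and the best guess is right 71% of the time. Single-centre conduct, open treatment and a published block size make those conditions plausible; the article does not establish them. Combined with a visual entry judgement that can be repeated in those judged unable, this gives an opportunity for selection bias, restricted by slow accrual and the day-30 limit.

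Nothing in the article shows that bias would occur, and its size in Motricity Index points cannot be derived from the document. Envelope handling is not at fault. The article contains no contradiction here; this is a design choice that can be improved cheaply.

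**What to change.** Have the independent statistician generate the list before the trial starts with block sizes drawn at random, for example from 4 and 6, or from 4, 6 and 8. Withhold the sizes from therapists and do not publish them until recruitment ends. The main gain is the loss of certainty, from 33% of allocations to about 6% or 2%. The plan should not claim that prediction is abolished, because the best guess remains near 69% or 67%.

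The cost is one new list and the possible small arm-size difference shown above. If exact balance matters more in so small a trial, sizes 4 and 6 are the milder choice.

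A minor addition: the pedalling verdict and set 2 baseline already precede allocation, so have the research therapist lodge them with the administrator before the envelope is opened. This makes the entry decision auditable. It does not prevent a prediction made before the verdict.

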## Background

### Therapy early after stroke

In the first few weeks after stroke, the brain is 'primed' for neurological recovery in response to rehabilitation training [1]. Indeed, Cramer [2] describes a 'golden period' for initiating restorative therapies, starting in the first days after onset and continuing for several weeks. However, animal studies on early therapy are equivocal. Kozlowski et al [3] demonstrated an increase in lesion size following early training and proposed a 'use-it-but-don't-overuse-it' strategy in this period. In contrast, Biernaskie et al [4] found that rats given enriched rehabilitation training from day five after an induced lesion demonstrated a marked improvement in recovery, whilst those given similar training beginning at day 30 improved no more than controls.

Whilst animal studies provide insights into brain changes underlying recovery, caution must be observed in generalising to human populations. Nonetheless, clinical studies do support early rehabilitation intervention to improve outcomes [5,6]. It is also possible that, if rehabilitation onset is delayed, patients might establish compensatory behaviours that could impact negatively on recovery of useful functional activity [7,8]. Additionally, National Clinical Guidelines for Stroke in the United Kingdom advise that people with acute stroke should be mobilised as early as possible [9]. However, the optimal dose and type of physical therapy required to drive useful functional reorganisation in early stroke survivors with different clinical characteristics remains unknown.

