### Participant inclusion criteria and recruitment process

Participants will be recruited from an acute stroke unit and, if necessary due to pressure on stroke beds, medical wards; in a University Hospital Trust. Consultant and therapy teams have agreed to support this trial.

Stroke survivors will initially be approached by a clinical team member responsible for their care, to check that they agree to speak to a researcher. If they agree, then a researcher will provide potential participants with verbal and written printed information about the trial. A video of the procedure for getting on and off the exercise cycle will also be available if patients wish to view it. A minimum of twenty four hours (1 working day) later, informed, signed consent will be sought. Those providing written informed consent will be participants in this trial. All potential participants will then be screened to check that they meet the study criteria, which are;

• adults aged 18+

• three to thirty days following a unilateral stroke resulting in unilateral muscle weakness with or without sensory deficit;

• fit to participate as assessed by a consultant-led medical team with resting oxygen saturations 95% or above, resting heart rate 90 beats per minute or less and systolic blood pressure of 100-160 mmHg

• score 0, 1 or 2 on the Functional Ambulation Categories [32]. Clinically, this means unable to walk; or need the help of two or more people; or require firm continuous or intermittent support of one person assisting with weight and balance;

• be able to sit unsupported for 30-seconds on the edge of a bed with feet on the floor.

• have sat out of bed in a chair or wheelchair at least once for a continual period of 15-minutes i.e. have appropriate sitting tolerance to participate in this cycling intervention;

• be able to follow a one-stage command i.e. sufficient communication, orientation and memory to participate in this cycling intervention;

• be independently mobile with or without an aid prior to the index stroke;

• have no co-existing pathology contributing to observed impairment in the paretic lower limb e.g osteoarthritis with associated knee deformity.

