### Measurement battery

Baseline measures will be made before randomisation and outcome measures after the intervention phase has been completed (figure 1). Baseline measures consist of two sets: prognostic indicators and clinical efficacy. Outcome measures will consist of clinical efficacy measures only.

The ***participant characteristics ***to be recorded for all potential participants and participants will be: gender, age (years), type and site of the stroke lesion (liaison with medical team from scanning/clinical findings) and time since stroke onset at entry to the trial and at each set of study measures (days).

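### Time since stroke, central to the trial's rationale and ranging from day 3 to day 30 at entry, is recorded but neither balanced at randomisation nor adjusted for in the stated primary comparison

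*Protocol article*

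**What the plan says.** - **Entry window.** Participant inclusion criteria and recruitment process: "three to thirty days following a unilateral stroke resulting in unilateral muscle weakness with or without sensory deficit".
- **Repeat attempts.** Study procedure: "Those unable to pedal and who are 30 days or less after stroke onset will be offered further pedalling assessments approximately every three days". Those who can pedal are randomised up to day 30, so the day of randomisation can fall well after the day of consent.
- **Allocation.** Study procedure: "Randomisation order will be generated before the trial begins by an independent statistician, in blocks of four". Envelopes are numbered in sequence and the next one is opened. No stratification factor or minimisation is named.
- **Analysis.** The Statistical Analysis section names independent t-tests between arms on follow-up measures with 95% confidence intervals, or non-parametric analogues. No covariate is named, not even the baseline value.
- **Data.** Measurement battery lists, among participant characteristics, "time since stroke onset at entry to the trial and at each set of study measures (days". Time since stroke is not one of the four prognostic indicators.
- **Rationale.** Background, Therapy early after stroke, presents the first weeks as a favourable period for training, and the Discussion repeats this. The Background cites one rat study with a clear benefit when enriched training started on day 5, "whilst those given similar training beginning at day 30 improved no more than controls". It also warns that "caution must be observed in generalising to human populations".

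**The concern.** A protocol that justifies an intervention by its timing has reason to protect the comparison against differences in timing. People at day 4 and day 29 may be at different stages of natural recovery. With at most 24 randomised, one arm can by chance sit several days nearer to onset than the other. The difference in follow-up Motricity Index would then partly reflect stage of recovery.

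The trial is run to decide whether larger studies are worthwhile. That decision is taken once, from one small sample, so the reliability of this particular draw matters as well as the long-run behaviour of the test.

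**Working it through.** **The plan's own figure.** Sample Size gives 2 participants per month for 12 months: 2 × 12 = 24, which reproduces. The Abstract counts 24 participants and randomises only those able to pedal, so 12 per arm is a ceiling. Equal allocation is assumed from two arms and blocks of four.

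**Assumptions (the protocol gives no figures).**
- Day of entry: uniform on 3 to 30, or early-skewed over the same range (3 + 27 × a Beta(1.5, 3) variable).
- Correlation ρ between days since stroke and follow-up Motricity Index: 0, 0.3, 0.5 or 0.7.
- Number randomised: 24, 16 or 12.

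**Step 1: size of chance imbalance.** Uniform entry has SD 27/√12 = 7.79 days. The early-skewed pattern has SD 5.43 days. With m per arm, the arm difference in mean days has SD = (SD of entry day) × √(2/m). For m = 12 and uniform entry this is 7.79 × √(2/12) = 3.18 days. Simulation of 100,000 trials with blocks of four gives:

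| Randomised | Entry | SD of arm difference (days) | P(gap > 5 days) |
|---|---|---|---|
| 24 | uniform | 3.18 | 11.7% |
| 24 | early-skewed | 2.22 | 2.4% |
| 16 | uniform | 3.89 | 20.1% |
| 16 | early-skewed | 2.71 | 6.5% |
| 12 | uniform | 4.50 | 27.0% |
| 12 | early-skewed | 3.14 | 11.1% |

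**Step 2: what a 5-day gap does to the unadjusted difference.** Shift in outcome SDs = ρ × 5 / (SD of entry day). With uniform entry:
- ρ = 0.3: 0.3 × 5/7.79 = 0.19
- ρ = 0.5: 0.5 × 5/7.79 = 0.32
- ρ = 0.7: 0.7 × 5/7.79 = 0.45

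For scale, the standard error of the arm difference with 12 per arm is √(2/12) = 0.41 SD, so these shifts are about 0.5 to 1.1 standard errors. With early-skewed entry the same correlations give 0.28, 0.46 and 0.64 SD, but gaps that large are much rarer.

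**Step 3: false-positive rate of the unadjusted t-test, no true effect, n = 24, uniform entry.**
- Over all trials: about 5% at every ρ.
- Among trials with a gap above 5 days: 8%, 13% and 22% at ρ = 0.3, 0.5 and 0.7.
- In those same trials after adjustment for days since stroke: 5.0%, 5.3% and 5.1%.

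**Step 4: precision after adjustment, n = 24.** The variance relative to the unadjusted estimate is about (1 − ρ²) × (1 + 1/(n − 4)), and 1 + 1/20 = 1.05.
- ρ = 0: 1.05
- ρ = 0.3: 0.91 × 1.05 = 0.96
- ρ = 0.5: 0.75 × 1.05 = 0.79
- ρ = 0.7: 0.51 × 1.05 = 0.54

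The simulated values are 1.05, 0.96, 0.79 and 0.54. These figures are for days since stroke alone. Once baseline Motricity Index is in the model, the further gain depends on the correlation that remains after it.

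**Step 5: stratified allocation, n = 24, uniform entry.** Two strata split at day 14 or day 16.5, with blocks of four, bring the SD of the arm difference to 1.83 or 1.76 days and P(gap > 5 days) to about 0.5%.

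**The case against.** The strongest reply is that randomisation already deals with this. Chance imbalance does not bias the comparison on average, the overall type I error stays near 5% in every scenario, and the confidence interval carries the variability. The protocol disclaims a definitive efficacy test and says that interpretation will reflect the small sample. All of that is right. What remains is avoidable loss of precision and a single result that may mislead.

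Several stronger readings are tempting, and the documents do not support them.

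- **A reader might infer that the protocol's own rationale implies strong response at day 3 and none at day 30.** That contrast comes from one rat study. The same section calls the animal evidence equivocal, cites another study in which early training enlarged the lesion, and describes a favourable period in people lasting several weeks, which covers much of the window.
- **A reader might turn a 5-day gap into Motricity Index points through an assumed gain per day.** The stated analysis compares follow-up levels, not gains. A later entrant may start higher and have less left to gain, so neither the sign nor the size in points is established.
- **A reader might infer that repeat attempts push weaker people to later entry.** The reasons given for re-testing are fear of movement and emotional distress, and the crank is meant to let people with marked weakness pedal.
- **Day 14 might seem a natural cut because the preliminary study started there.** That was an eligibility limit (day 14 or later), not a biological threshold.

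It is also fair to say that, with 24 or fewer, paresis severity, lesion site and walking ability have comparable claims to a single stratification factor. Stratification is therefore optional. Finally, this is not detail left to an unseen analysis plan: the article itself fixes both the allocation method and the between-arm test.

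**Conclusion.** The point holds as a worthwhile, inexpensive improvement to an analysis that the protocol fixes. It is neither an error nor a source of systematic bias. Its size rests on two things the protocol does not give: the spread of entry days, which moves the chance of a gap above 5 days at full enrolment from about 12% down to about 2%, and the correlation of days since stroke with outcome. If that correlation is near zero, the imbalance does no harm and adjustment costs a little. At 0.3 to 0.7, adjustment removes 4% to 46% of the variance with 24 randomised. The case strengthens if fewer are randomised and imbalance becomes more common, although with 12 randomised and a correlation of 0.3 adjustment no longer gains precision (variance ratio 1.03).

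**What to change.** In Statistical Analysis, replace the unadjusted t-test for the primary outcome with a prespecified ANCOVA of follow-up Motricity Index on arm, baseline Motricity Index and days from stroke to randomisation. Report the adjusted difference with its 95% confidence interval. Name a rank-based ANCOVA with the same covariates as the fallback if normality fails, so that the adjustment is not lost there.

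The data are already collected and no trial procedure changes. Days since stroke cost one degree of freedom, and about 5% more variance with 24 randomised if they are unrelated to outcome (about 8% with 16). Baseline Motricity Index uses one further degree of freedom.

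Optional, and only if the trial has not started: two envelope series split at one prespecified day since stroke, each in blocks of four. The cost is a second series and a possible incomplete block in each stratum. The cut should be stated as a practical choice.
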